### Intervention

Patients in the real CBM condition will conduct a treatment version of the Food Approach-Avoidance Task (Food-AAT) [39]. In this task, participants are shown colour photographs of food and control (i.e. neutral household and office) items on a computer screen. They are required to pull or push a joystick in response to the outline of the picture (round versus rectangular), irrespective of picture content. Format movement assignments are counterbalanced among participants (i.e. half will push round pictures and half will push rectangular pictures). When the joystick is pulled, the picture grows bigger and when it is pushed it grows smaller. This zooming-in and zooming-out emphasises respective sensations of approaching and avoiding and thus combines the proprioceptive (arm movement) and exteroceptive (zooming feature) cues of approach and avoidance behaviour [47]. The treatment version of the Food-AAT adopts an implicit learning paradigm by presenting all food pictures in the ‘push’ (i.e. avoid) format so that participants learn to link avoidance movements to visual cues of high-calorie food. Patients will receive ten 15-min sessions of training over a 4-week period.

Patients in the control condition (sham CBM) will receive the same dosage of the same task but will *not* be trained to avoid food cues in the Food-AAT. Instead, patients in the control condition receive 10 additional sessions of the pre- and post-treatment assessment version of the task (Food-AAT), which requires an equal number of approach and avoidance movements to both food and non-food pictures. Sham (placebo) CBM with an equal dosage, frequency and character was chosen as the comparator treatment in order to examine the specific effects of this form of CBM.

Sessions will take place in dedicated research facilities. In line with the vulnerability-stress model of cognitive biases described in the introduction [48], participants will be presented with a set of pictures that are considered to induce mild levels of negative mood at the beginning of every training session (60 images; duration: approximately 1 min) [49].

Study adherence: a researcher will be present throughout the training and assessment sessions to ensure study adherence. The interventions are predefined, computerised tasks. Any deviation from the study protocol will be recognised and recorded immediately. We will ask participants to refrain from any other treatment that focuses on their eating disorder. However, if clinical need dictates another treatment, this will be documented but will not lead to the exclusion of the participant. Participants are allowed to discontinue the treatment at any time.

### Procedure

A flowchart outlining the study procedures is presented in Fig. 1. For further information about the time schedule of enrolment, interventions and study assessments, please see Table 1.

#### Screening

Potential participants will be referred to the study by their clinician or by themselves. Study researchers will screen participants for eligibility. Screening includes the Structured Clinical Interview for DSM Disorders (SCID) [50–52], a short inclusion/exclusion screen specific to this study, and an assessment of medical and psychiatric history and medication dosage and stability. In line with the Consolidated Standards of Reporting Trials (CONSORT) guidelines, we will record the number and reasons for any participants we must exclude, or any who decline consent or withdraw from the study.

#### Baseline assessment

Binge-eating frequency and general eating disorder symptomatology will be assessed in terms of a specific, structured clinical interview, i.e. the Eating Disorders Examination [53, 54]. Participants will also be weighed and asked to complete a battery of questionnaires relating to eating disorder symptomatology, food craving, depression and anxiety, as well as neuropsychological computer tasks that assess approach bias and attentional bias towards visual food cues and working memory. Furthermore, state levels of food craving after cue exposure and food intake will be assessed in laboratory tasks.

Once the baseline assessment is completed, participants will be randomly allocated to the treatment (real CBM) or control (sham CBM) group. Randomisation will be performed independently from the trial team by a central study office at Heidelberg University Hospital. The first CBM session will start on the day of the baseline assessment. Participants in the sham group will be offered the opportunity to receive real CBM after the end of follow-up.

#### Post-treatment assessment

The post-treatment assessment will take place after the last training session, and will include the same elements as the baseline assessment except for the Eating Disorders Examination.

#### Two-month follow-up

Two months after the post-treatment assessment a follow-up session will be conducted which will involve the Eating Disorders Examination. Finally, the success of blinding will be evaluated by asking participants to guess the treatment allocation. Participants will be unmasked and individuals in the control group will then be offered the real treatment.

### Measures

#### Screening measures

▪ Body Mass Index (kg/m^2^)▪ Screening module of the SCID [50–52]: this semistructured psychiatric interview will be used as a diagnostic screen to assess the presence of psychiatric comorbidities.▪ The depression module of the Patient Health Questionnaire (PHQ-9) [55, 56] and the General Anxiety Disorder Screener-7 (GAD-7) [57, 58] are reliable and valid as well as widely used self-report instruments to assess symptoms of depression and anxiety according to the DSM-5.

#### Primary outcome measure

▪ Eating Disorder Examination (EDE) [53, 54]: the primary outcome variable in this study is the treatment-specific change from baseline to 2-month follow-up in the number of objective binge-eating episodes as assessed by the EDE. The EDE is a reliable and valid as well as widely used measure of eating disorder symptoms and is regarded as the instrument of choice for the assessment and diagnosis of eating disorders according to the DSM-5.

#### Secondary outcome measures

▪ Food Approach-Avoidance Task (Food-AAT), assessment version [16, 39, 59]: this task will be used to assess approach bias towards visual cues of high-calorie food (expected target cognitive mechanism of intervention). It is identical to the treatment version except that in the assessment version of the task, the required response is unrelated to the picture content (i.e. food and neutral stimuli are presented equally often in round and rectangular, i.e. push and pull, format). The approach bias towards food is calculated by subtracting the median reaction time (RT) for pulling food pictures from the median RT for pushing pictures of this category [59]. Thus, a positive value denotes an approach bias (i.e. the participant is faster in pulling than in pushing food pictures), whereas a negative value indicates an avoidance bias.▪ Visual probe task [60]: this task will be used to assess participants’ attentional bias towards visual food cues. During this computer task picture pairs (food/non-food) are presented side by side on a computer screen after the presentation of a fixation point at the centre of the screen and are followed by the presentation of a probe (denoted by *) appearing in the location of one of the pictures. Participants are instructed to indicate the location of the probe by pressing a corresponding key on a keyboard as quickly as possible. The position of the food and neutral pictures are balanced across trials so that each appears in either location with equal frequency. Recordings of the participant’s manual response latency when indicating the location of the probe are used to calculate a response latency bias. The logic of this task presumes that participants who have an attention bias towards food are quicker in responding to indicate the location of the probe when the probe replaces a food stimulus. Thus, the latencies of manual responses provide an index for attention bias for food. Positive values indicate faster mean latencies (i.e. an attentional bias) to food cues than for neutral cues.▪ The Food Challenge Task [16, 39, 61]: the Food Challenge Task will be used to examine cue-induced food craving. Participants rate their state levels of food craving using the Food Cravings Questionnaire State Version [62, 63] after being presented with filmed cues of highly appetitive foods.▪ Taste Test: food intake will be measured by means of a ‘Taste Test’. Participants will be instructed to rate three bowls of highly palatable food items (chocolate, crisps, fruit gums) in terms of their visual attractiveness, smell and taste. The participants will be told that they are free to try as much of the offered items as they like. Consumption will be determined by weighing the bowls both before and after the Taste Test.▪ The digit-span forward and backward subtests of the Wechsler Memory Scale III [64] will be used to measure working memory capacity.▪ Global eating disorder psychopathology will be assessed by the EDE [53, 54].▪ The Food Cravings Questionnaire Trait Version [62, 63]: this is a reliable and valid self-report questionnaire that measures trait levels of craving for food.▪ Treatment acceptance will be assessed using a feedback form composed of several standard questions regarding the acceptance of the intervention [39].

Confidentiality and anonymity of all personal data will be retained throughout the entire study. Manual files will be securely locked in a lockable filing cabinet and all electronic files will be password-protected. Identifying information will be removed from the data, stored separately and replaced with a numeric identification code. The master list of names which correspond to each participant’s numeric identification code will be stored electronically and will be password-protected. This information will only be accessible to key researchers involved in the study.

### Randomisation

Randomisation will be performed independently from the trial team by a central study office at Heidelberg University Hospital using a specific randomisation software (RANDI2). Randomisation will be stratified for BN and BED in a 1:1 ratio. Participants in the sham group will be offered the opportunity to receive real CBM after the end of follow-up.

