## Methods

### Design

This is a superiority trial adopting a double-blind, randomised, placebo-controlled, parallel-group design comparing real and sham CBM. Participants with BN or BED will be randomly allocated to receive either 10 sessions (15 min each) of real CBM (treatment group) or sham CBM (control group) in a period of 4 weeks. Participants will be recruited from two different sites (Heidelberg, Germany and London, UK). Outcomes will be assessed at baseline, post-treatment and 2-month follow-up. The study protocol is outlined in the flow chart in Fig. 1, and Table 1 provides details of all assessments at the different timepoints.

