### Sample size

Previous randomised controlled trials comparing real and sham versions of approach bias modification in clinical samples applied a repeated measures ANOVA design (group × time) to examine treatment-specific changes and have reported small-to-medium effect sizes (η_p_^2^ between 0.05 and 0.06) [27, 29, 30]. Using the smallest effect size that has previously been reported, a total sample size of 40 patients will have 80 % power to detect an effect of this size using a 2 × 2 repeated measures ANOVA with a 0.05 two-tailed significance level. The percentage of data lost owing to errors in the applied neuropsychological tasks was 7 % at the maximum in previous studies. Taking this and a potential dropout rate of 25 % into account, a minimum of 53 patients must be included. Thus, we will recruit 27 patients for each group (total *n* = 54).

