### Analyses

To determine quality, completeness and variability of the outcome measures, descriptive statistical analyses and graphical methods will be used. To evaluate treatment-specific changes over time in patients, a 2 × 2 repeated measures ANOVA, with group as between-subject factor and time as within-subject factor, will be applied. The size of the treatment effect on the outcome measure (EDE) will be the difference in outcome data between those in the two treatment conditions at follow-up. Additionally, multiple regression models will permit exploration of the relationship between changes in the cognitive measures and symptom improvement. No interim analyses are planned. A two-tailed significance level of *p* < .05 will be used throughout. Both completer and intent-to-treat analyses will be performed. Missing values will be replaced by using the Last Observation Carried Forward (LOCF) method for the intent-to-treat analysis. As this is a pilot trial resources do not stretch to setting up a Monitoring Committee. Analyses will be conducted by the principal investigators. As CBM is a safe procedure with no known side effects we do not expect any unexpected adverse reactions, serious or unexpected serious adverse reactions. We will report any adverse reactions and serious adverse events. It is intended that the results of the study will be reported and disseminated by the principal investigators at international conferences and in peer-reviewed scientific journals.

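### Randomisation is stratified by diagnosis, but the fixed 2 × 2 ANOVA leaves the stratum out, so the primary test may be conservative and forgo some power

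*Protocol article*

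**What the plan says.** The Randomisation section reads "Randomisation will be stratified for BN and BED in a 1:1 ratio". Diagnosis is the only stratification factor named. Under Design the article says "Participants will be recruited from two different sites", but site is not mentioned as a factor in the randomisation.

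The Analyses section specifies a 2 × 2 repeated measures ANOVA, "with group as between-subject factor and time as within-subject factor, will be applied". The Sample size section uses the same 2 × 2 model, at a "0.05 two-tailed significance level". With two levels each for arm and time, the model has no place for a diagnosis term.

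Two quantities come out of this analysis. The primary outcome is the "treatment-specific change from baseline to 2-month follow-up in the number of objective binge-eating episodes", which the group × time interaction tests. The size of the effect, however, "will be the difference in outcome data between those in the two treatment conditions at follow-up", with no adjustment mentioned for it.

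**The concern.** Stratified allocation makes the arms alike in their mix of BN and BED. The arm difference then varies less from one randomisation to the next than it would under unrestricted allocation. An analysis without the stratum still counts the BN/BED variation as error, so it reports a standard error larger than the one the design delivers. Confidence intervals come out too wide and the test rejects too rarely under the null. The benefit of stratifying is paid for in the design and not collected in the analysis.

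This is not a detail left to a later analysis plan. The article names the factors of the model, and a plan that added the stratum would depart from what has been published. Precision matters here because the calculation needs 40 analysable patients for 80% power and 54 are to be recruited.

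**Working it through.** **Inputs from the article:** partial η² = 0.05 (the smallest reported), two-sided α = 0.05, 80% power, N = 40 before losses, 25% dropout.

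**Assumptions (not in the article):** pre–post correlation ρ = 0.5; the share R² of the variance of change explained by diagnosis, varied from 0 to 0.30; two equal strata with exact 1:1 balance in each.

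**Step 1, the planned N.**
- f² = 0.05/0.95 = 0.0526.
- Noncentrality λ = f² × N × m/(1 − ρ) = 0.0526 × 40 × 2/0.5 = 8.42, with 1 and 38 degrees of freedom.
- Power = 0.807, so the stated 40 is reproduced under ρ = 0.5.
- The group × time test is the same as a t test on change scores. The matching standardised difference is √(4λ/N) = √(4 × 8.42/40) = 0.918.

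**Step 2, approximate effect of leaving out a balanced stratum.** The true variance of the arm difference is (1 − R²) times the variance that the model estimates.
- The model's standard error is therefore too large by the factor 1/√(1 − R²).
- The true type I error is 2 × [1 − Φ(1.96/√(1 − R²))].
- For R² = 0.05, 0.10, 0.20 and 0.30 the factor is 1.026, 1.054, 1.118 and 1.195, and the type I error is 0.044, 0.039, 0.028 and 0.019.

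**Step 3, simulation of the change-score test at N = 40** (60,000 runs per setting; total variance of change held fixed):

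| R² of change | Type I error, stratum omitted | Type I error, included | Power, omitted | Power, included |
|---|---|---|---|---|
| 0 | 0.049 | 0.049 | 0.80 | 0.80 |
| 0.05 | 0.045 | 0.050 | 0.81 | 0.82 |
| 0.10 | 0.039 | 0.051 | 0.82 | 0.85 |
| 0.20 | 0.028 | 0.051 | 0.83 | 0.88 |
| 0.30 | 0.019 | 0.050 | 0.84 | 0.92 |

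At R² = 0.10 the model's standard error averages 0.315 against a true value of 0.300. At R² = 0.20 it is 0.316 against 0.284.

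**Step 4, site, not stratified.** With site omitted, type I error is 0.052 at R² = 0.10 and 0.051 at R² = 0.20, and the model's standard error (0.314) agrees with the true one (0.317). Including site raises power from 0.81 to 0.84 and from 0.81 to 0.88 respectively. This is a gain in precision, not the repair of an error rate.

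**Step 5, which term does the work.** In one simulated data set (N = 40, diagnosis affecting level and change), the standard error of group × time was 0.3951 without diagnosis, 0.3951 with diagnosis as a time-constant term, and 0.3630 once diagnosis × time was added.

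**The case against.** The strongest reply is that the loss is conditional and never anti-conservative.

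- **Only change matters for the primary test.** A constant BN/BED difference in binge frequency cancels in the group × time interaction. If the two diagnoses change alike, nothing is lost. This stands. It does not cover the follow-up difference that the article reports as its effect size, where a difference in level enters the error directly.
- **The effect needs balance within strata.** The article does not describe blocking, and a condensed article need not. Under simple allocation within strata, simulated type I error is 0.049 at R² = 0.10 and 0.051 at 0.20, which is nominal. With balanced strata and 25% random dropout it is about 0.041 and 0.034, milder than in the table. This also stands. However, stratification without some balancing within strata would serve no purpose, so near-balance is the natural reading.
- **Planned power is not undercut.** Unadjusted power is at or above 80% at every R² examined, under the article's own assumptions. What is lost is a gain that could have been had. The trial also describes itself as a pilot.

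A reader might also infer that leaving out site distorts the error rate, since the sites are in two countries with two languages. The documents do not support this. Site is not a stratification factor, and chance imbalance in an unstratified covariate is ordinary sampling variation that the unadjusted standard error already covers.

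**Conclusion.** The point holds in a conditional form. The article stratifies by diagnosis and fixes a model that excludes it. Given near-balance within strata and some relation between diagnosis and change (or level, for the follow-up difference), the standard error is overstated and the test is conservative. Under R² of 0.05 to 0.30, the power forgone at N = 40 runs from about 1 point (0.81 against 0.82) to about 8 points (0.84 against 0.92). At R² = 0 it is nil.

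The R² values are assumptions. The choice of diagnosis as the stratification factor suggests that it was thought prognostic, but this gives no figure. Two stronger readings should be set aside: that the standard error is certainly wrong, and that the risk is one of false positives. The first depends on a quantity that the article does not give. The second has the direction reversed, because any error takes the type I rate below 0.05.

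**What to change.** Add the BN/BED stratum and its interaction with time to the primary repeated measures model, and use the same model for the secondary outcomes. Adjust the between-arm difference at follow-up for the stratum. The interaction with time must be named, because a diagnosis term that is constant over time leaves the group × time standard error unchanged.

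Site may be added in the same way, with its interaction with time, as an optional precision covariate; if it is wanted, say so in advance.

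The cost is a sentence of text and about one degree of freedom (38 to 37 at N = 40), plus one more if site is included. Diagnosis is known at randomisation and site at recruitment, so no new data are needed. In the simulation, including the stratum when it predicts nothing left power at 0.80.

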### Blinding

Participants and assessors using the EDE will be blinded to treatment allocation throughout, i.e. the study will be conducted in a double-blind fashion. To assess whether allocation concealment has been successful, participants will be asked to guess the treatment allocation at the end of treatment and to indicate how certain they are of this guess. Participants will be debriefed and unblinded to group allocation upon completion of the 2-month follow-up.

### Analyses

To determine quality, completeness and variability of the outcome measures, descriptive statistical analyses and graphical methods will be used. To evaluate treatment-specific changes over time in patients, a 2 × 2 repeated measures ANOVA, with group as between-subject factor and time as within-subject factor, will be applied. The size of the treatment effect on the outcome measure (EDE) will be the difference in outcome data between those in the two treatment conditions at follow-up. Additionally, multiple regression models will permit exploration of the relationship between changes in the cognitive measures and symptom improvement. No interim analyses are planned. A two-tailed significance level of *p* < .05 will be used throughout. Both completer and intent-to-treat analyses will be performed. Missing values will be replaced by using the Last Observation Carried Forward (LOCF) method for the intent-to-treat analysis. As this is a pilot trial resources do not stretch to setting up a Monitoring Committee. Analyses will be conducted by the principal investigators. As CBM is a safe procedure with no known side effects we do not expect any unexpected adverse reactions, serious or unexpected serious adverse reactions. We will report any adverse reactions and serious adverse events. It is intended that the results of the study will be reported and disseminated by the principal investigators at international conferences and in peer-reviewed scientific journals.

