### Aims

The central aim of this randomised controlled pilot trial is to examine whether a specifically tailored, brief (10 sessions), computerised CBM training (approach bias modification versus sham) is able to reduce binge-eating episodes in BN and BED patients (primary efficacy endpoint). More precisely, from pre-treatment to 2-month follow-up, BN and BED patients who receive real CBM are expected to report a greater reduction in the number of objective binge-eating episodes during the previous 2 months than those who receive sham CBM.

Additionally, we will investigate whether this CBM programme reduces global eating disorder psychopathology from pretreatment to follow-up, and trait and cue-elicited food craving, food intake and approach and attentional bias towards visual food stimuli in BN and BED patients from pre- to post-treatment. Finally, we will assess treatment acceptance by attrition rates and by means of a specifically designed feedback form. Specifically, as compared to patients in the sham CBM condition, patients in the real CBM condition are expected to show (1) decreased global eating disorder psychopathology from pre-treatment to follow-up, (2) decreased approach and attentional bias towards food cues, (3) decreased state food craving after cue exposure, (4) decreased trait food craving as well as (5) reduced food intake in a bogus taste test from pre- to post-treatment. In an exploratory analysis we will examine the patients’ acceptance of this specific CBM intervention, taking dropout rates and scores on a feedback form into account (treatment acceptance).

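### The primary binge-episode count is tested by an unadjusted group-by-time ANOVA, with no baseline adjustment and no other scale stated; validity holds, but power is lost

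*Protocol article*

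**What the plan says.** The Primary outcome measure section defines the endpoint as treatment-specific "change from baseline to 2-month follow-up in the number of objective binge-eating episodes as assessed by the EDE". The Aims give the counting window and the hypothesis: a "greater reduction in the number of objective binge-eating episodes during the previous 2 months" with real than with sham training.

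The Analyses section names one between-group test, a 2 × 2 "repeated measures ANOVA, with group as between-subject factor and time as within-subject factor, will be applied". The size of the treatment effect "will be the difference in outcome data between those in the two treatment conditions at follow-up". The Sample size section builds on the same 2 × 2 model.

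The article names no covariate, transformation, count model or robust alternative. It does plan a descriptive step ("To determine quality, completeness and variability of the outcome measures, descriptive statistical analyses and graphical methods will be used") but attaches no consequence for the model. BN and BED patients are pooled, and the Randomisation section stratifies by diagnosis; the stratum does not appear in the stated analysis.

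**The concern.** An episode count cannot go below zero, its variance usually rises with its mean, and a patient's possible absolute reduction is capped by the baseline count. With two groups and two times, the group-by-time F test is the square of the t-test on follow-up minus baseline. That test fixes the coefficient of baseline at 1. If the within-patient correlation is moderate or treatment acts proportionally, this coefficient is too large, and the baseline noise of high-frequency patients enters the error term in full.

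What is at stake is efficiency on the primary endpoint with about 40 evaluable patients. A null result could reflect the analysis and not the training. The baseline count and the diagnosis are collected anyway, so leaving them out of the model saves nothing.

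**Working it through.** **1. The plan's own figure.** Inputs from Sample size: η² "between 0.05 and 0.06", the smaller value taken ("Using the smallest effect size that has previously been reported"), and a "0.05 two-tailed significance level". Assumption: within-person correlation ρ = 0.5, which the article does not state.

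- f² = 0.05/0.95 = 0.0526
- λ = f² × N × 2/(1 − ρ) = 0.0526 × 40 × 2/0.5 = 8.42, with 1 and 38 df
- Power = 0.807, so N = 40 reproduces.

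This is a normal-theory figure for a standardised effect. It contains nothing about the spread of episode counts.

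**2. Assumed count model.** The article gives no mean, SD, correlation or dispersion for episodes, so all of the following is assumed. Counts are Poisson around a mean multiplied by a patient-level gamma frailty (shape a) and a visit-level gamma frailty (shape c). Baseline mean is 24, sham follow-up mean 18, rate ratio 0.6 (real follow-up mean 10.8), with 20 per arm.

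With k = (1 + 1/a)(1 + 1/c) − 1, the variance at mean m is m + k·m², and the covariance between visits is m₁m₂/a.

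**3. Raw change by hand, shapes 2/3.**
- k = 1.5 × 1.333 − 1 = 1
- Baseline variance 24 + 576 = 600 (SD 24.5). Follow-up variance: sham 18 + 324 = 342; real 10.8 + 116.6 = 127.4
- Variance of change: sham 600 + 342 − 2 × 216 = 510; real 600 + 127.4 − 2 × 129.6 = 468
- Pooled SD = √489 = 22.1. Mean difference in change = 18 − 10.8 = 7.2, or 0.326 SD
- Noncentrality = 0.326 × √(20/2) = 1.03, so t-test power on 38 df is about 17 %. Simulation gives 18 %.

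**4. Simulated power, proportional effect** (6,000 trials per row; independent repeats agree within about 3 percentage points)

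| Shapes (baseline SD) | Raw change | Log(1 + count) change | Raw ANCOVA | Log ANCOVA |
|---|---|---|---|---|
| 4/4 (19) | 25.3 % | 44.8 % | 55 % | 56.3 % |
| 2/3 (25) | 18.5 % | 34.4 % | 38 % | 42.3 % |
| 1.5/2 (30) | 13.4 % | 24.7 % | 26 % | 30.9 % |

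Share of the total gain that baseline adjustment alone recovers on raw counts:
- 4/4: (55 − 25.3)/(56.3 − 25.3) = 96 %
- 2/3: (38 − 18.5)/(42.3 − 18.5) = 82 %
- 1.5/2: (26 − 13.4)/(30.9 − 13.4) = 72 %

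**5. Equal absolute falls (5 sham, 13 real).** With the same frailty shapes, raw ANCOVA reaches 12–26 % and log ANCOVA 30–53 %. A second set of assumptions (mean parameter 25, baseline of at least 8, fall taken from the patient's mean; low, medium and high dispersion) gives:
- raw change 35 / 17 / 11 %
- raw ANCOVA 50 / 25 / 15 %
- log ANCOVA 70 / 53 / 37 %

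The levels depend on how the fall is modelled. The ordering does not, and here the log scale supplies the larger part.

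**6. Sensitivity.** Under the second set with falls of 30 % v 65 %, raw change has 42 % power at lower dispersion and 19–21 % at high dispersion; raw ANCOVA has 88–91 % and 46–51 %. With almost no overdispersion, raw change reaches 69–90 % and the log-scale and baseline-adjusted analyses 91 % or more. Raw change was weaker than these alternatives in every scenario.

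**7. Type I error.** Raw change rejects in 4.0–5.2 % of null trials across the runs. Log change and log ANCOVA also stay near 5 %.

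**The case against.** **The scale is inferred from silence.** The article does not say that counts stay untransformed, it condenses a fuller protocol, and transformations are often left to an analysis plan. This stands as a limit: one can say only that no other scale is stated. It does not remove the point, because the outcome, the test and the effect measure are all named, and the named test is an unadjusted comparison of change on whatever scale is used.

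**The count scale is not the main culprit.** A reader might credit the log transform with the whole rise from about 18 % to about 42 %. The table does not support that: under proportional effects, ordinary ANCOVA on raw counts already gets most of the way and keeps the stated difference in episodes as the effect measure. This stands, and it is why the fix leads with baseline adjustment. The log scale still helps on its own (18.5 % to 34.4 % for change scores), and it matters most under equal absolute falls.

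**Nothing is invalid.** Correct: at equal arm sizes the null rejection rate is nominal, and the trial is described as a pilot. But the article also calls it a superiority trial with a directional hypothesis on this endpoint, so efficiency still matters.

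**Outliers.** A reader might infer that one or two patients can decide the result. That was not shown. The 4 of 40 patients with the largest deviations carry 53–67 % of the within-group sum of squares of change, but the figure is already 44 % for near-Poisson counts, and no leave-one-out check was done. This is concentration of variance, not evidence that a result would reverse.

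**Conclusion.** The point holds as a loss of efficiency in a stated method. The planned test ignores the baseline count as a covariate and works on a scale poorly suited to a skewed, zero-bounded count. Under the assumed proportional effect, baseline adjustment roughly doubles power; under equal absolute falls, most of the improvement needs the log scale.

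The direction was consistent across all assumptions tried. The size cannot be taken from the documents: it rests on assumed means, dispersion, effect form and 20 evaluable patients per arm. Nor do these percentages refute the plan's 80 %, as a reader might infer. That figure is for a standardised effect taken from earlier trials, whereas the simulations impose an effect on episodes. In most overdispersed scenarios power stays below 80 % even with the better analysis, so the change improves the trial without making it well powered.

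**What to change.** Before outcome data are examined by arm, specify the primary analysis as a regression of follow-up episodes on arm, baseline episodes and diagnosis stratum (BN/BED), preferably with both counts as log(1 + count). Report the arm effect as a ratio with its 95 % CI, and give the baseline-adjusted mean difference in episodes alongside, so that the effect measure stated in Analyses is kept. A negative binomial model is not an automatic improvement at this size: its Wald test rejected in 9.6 % of simulated null trials with 20 per arm.

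The cost is wording only: no extra patients, visits or measures. Recruitment has begun, but no interim analysis is planned. Participants are unmasked individually after follow-up, so the date of the change should be recorded against the first comparison of outcomes by arm. The small downside is that the log-scale effect is a ratio, which depends slightly on the added constant, and not a difference in episodes.
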